## Abstract

**Background:**

Opioids and epidural analgesia are a mainstay of perioperative analgesia but their influence on cancer recurrence remains unclear. Based on retrospective data, we found that cancer recurrence following colorectal cancer surgery correlates with the number of circulating tumor cells (CTCs) in the early postoperative period. Also, morphine- but not piritramide-based postoperative analgesia increases the presence of CTCs and shortens cancer-specific survival. The influence of epidural analgesia on CTCs has not been studied yet.

**Methods:**

We intend to enroll 120 patients in four centers in this prospective randomized controlled trial. The study protocol has been approved by Ethics Committees in all participating centers. Patients undergoing radical open colorectal cancer surgery are randomized into epidural, morphine, and piritramide groups for perioperative analgesia. The primary outcome is the difference in the number of CTCs in the peripheral blood before surgery, on the second postoperative day, and 2–4 weeks after surgery. The number of CTCs is measured using molecular biology methods. Perioperative care is standardized, and relevant data is recorded. A secondary outcome, if feasible, would be the expression and activity of various receptor subtypes in cancer tissue. We intend to perform a 5-year follow-up with regard to metastasis development.

**Discussion:**

The mode of perioperative analgesia favorably affecting cancer recurrence would decrease morbidity/mortality. To identify such techniques, trials with long-term follow-up periods seem suboptimal. Given complex oncological therapeutic strategies, such trials likely disable the separation of perioperative analgesia effects from other factors. We believe that early postoperative CTCs presence/dynamics may serve as a sensitive marker of various perioperative interventions´ influences on cancer recurrence. Importantly, it is unbiased to the influence of long-term factors and minimally invasive. Analysis of opioid/cannabinoid receptor subtypes in cancer tissue would improve understanding of underlying mechanisms and promote personalization of treatment. We are not aware of any similar ongoing studies.

**Trial registration number:**

NCT03700411, registration date: October 3, 2018. Study status: recruiting.

## Background

Colorectal cancer (CRC) is the second most common cause of cancer-related deaths in Europe. Despite the progress in its early detection and adjuvant treatment, metastases are the leading cause of death in this group of patients. Although the development of postoperative metastases is a multifactorial process, it has been suggested that the mode of perioperative analgesia (PA) may play an important role in cancer recurrence (CR) [1, 2]. It has been proposed that avoiding opioids (particularly morphine) and employing regional analgesia techniques may have favorable effects on CR [1]. Such effects, if present, are probably attributable to less suppression of antitumor immune defenses due to:Better analgesia leading to a less pronounced perioperative stress reaction [1] which preserves anticancer immunity (particularly natural killer cells’ cytotoxicity). Such effects of epidural analgesia have been observed in open colectomy [3] and other major abdominal surgeries [4].Reduced exposition to volatile and intravenous anesthetics [1].Reduced exposition to opioids, especially morphine which exhibits negative effects on anticancer immunity and increases cancer cell proliferation, tumor progression [5, 6], and CR [2, 5, 7–10]. However, data on angiogenesis [8, 11–14] and cancer cell invasion [15, 16] are conflicting and some studies even show favorable immunomodulation [8].Positive effects of local anesthetics (cytotoxic and anti-proliferative). Indeed, promising results of in vitro [17] and animal studies showed that regional anesthesia decreases the risk of metastasis [5, 18, 19].

During the last 15 years, several retrospective and post-hoc analyses yielded conflicting results regarding the effects of PA on cancer recurrence following CRC surgery. Christopherson et al. observed that epidural analgesia was associated with improved survival in CRC patients without metastases. However the effect lasted for only 1.46 years postoperatively, may have been caused by a reduction in early postoperative adverse events and the data come from 1992–1994 rendering them less relevant for current treatment standards [20]. In post-hoc analysis, Gottschalk et al. observed the potential benefits of epidural analgesia but limited only to patients > 64 years [21]. Gupta et al. observed a reduction in all-cause mortality after rectal but not colon cancer surgery using epidural analgesia but the mean follow-up was short (2.6 years) and actual causes of death were unknown [22]. More recently, Zimmitti et al. showed that epidural analgesia improved recurrence-free survival and overall survival in patients undergoing hepatic resection for liver metastases despite significantly longer operative times compared to the control group [23]. Also, Vogelaar et al. observed improved five-year survival in the epidural analgesia group of CRC surgical patients and this effect was even more significant in a subgroup of patients > 80 years [24]. In an in vitro study, Xu et al. found that the serum from colon cancer patients receiving propofol and epidural analgesia inhibited proliferation and invasion of LoVo colon cancer cells and induced apoptosis more than in patients receiving sevoflurane anesthesia with opioid analgesia [25]. This finding shows that type of anesthesia and PA may affect the immune response and/or cancer cell biology potentially leading to a lower risk of metastasis in CRC.

On the other hand, in a large study in 42 151 patients undergoing colectomy for CRC, Cummings et al. found no improvement in CR in the epidural analgesia group (despite the fact that patients receiving epidural analgesia had better 5-year survival) [26]. Recently, Wu et al. observed no favorable effect of epidural analgesia on CR following curative colon cancer surgery in a single-center trial [27]. Likewise, Hasselager et al. found no CR benefit when analyzing 11 618 patients undergoing curative CRC surgery [28]. However, in both these trials, both open and minimally invasive surgery patients were included and patient recruitment stretched over long periods of time. The latter trial included also rectal cancer patients who received epidural analgesia more often. Also, Falk et al. published two negative findings in CRC surgery patients—in a retrospective analysis of more than 5700 patients undergoing both open and minimally invasive curative surgery, no survival benefit was observed in the epidural analgesia group at 30 days, 90 days, and 3 years [29]. In the only available prospective randomized multicenter trial comparing epidural analgesia and morphine-based analgesia in a mixed open and minimally invasive surgery population, Falk et al. found no statistically significant difference in disease-free survival [30]. However, a 7% improvement in disease-free survival was detected in the epidural analgesia group but the trial was underpowered to reach statistical significance. Moreover, the trial had to be stopped prematurely due to recruitment problems related to the increasing number of minimally invasive surgeries.

Clearly, a major limitation of the clinical trials studying CR is the long follow-up needed to assess survival outcomes. Effects of complex (and changing) oncological therapeutic strategies employed in colorectal and other cancers complicate the separation of PA effects from those of other interventions. And, adding to the complexity of various perioperative factors, anesthetics such as sevoflurane and propofol may also promote anticancer activity through the modulation of microRNA molecules that control post-transcriptional gene regulation [31]. Thus, based on the available data, it is difficult to recommend an optimal type of PA (and anesthesia) for CRC patients. Prospective trials employing methods enabling the assessment of PA effects independently of other factors are needed.

### Circulating tumor cells as the markers of CR

Following radical surgery, metastatic potential persists in the form of circulating tumor cells (CTCs) and disseminated tumor cells (DTCs) [32]. These cells may develop into macroscopic metastases [33, 34]. The process is likely accelerated by postoperative immunosuppression lasting for several days [35]. Interactions between the immune system and cancer cells are complex involving non-specific (natural killer cells, macrophages, neutrophils) as well as antigen-specific immune cells [32]. Both cancer and immune system cells are influenced by analgesic techniques [2].

We propose that CTCs presence and dynamics may serve as a sensitive surrogate biomarker of the effects of various perioperative factors (including analgesic techniques) on CR and survival. In CRC patients, it has been shown that CTCs presence during the first postoperative weeks is an independent negative prognostic factor [36, 37]. Our study group also found that morphine- but not piritramide-based analgesia increases CTCs presence [38], which may be attributable to different effects of piritramide and morphine on cell membrane receptors. Therefore, we believe that it is necessary to study the effects of PA on the presence of CTCs as well as on membrane receptors expressed on tumor tissue cells in order to personalize for the right patient at the right time. To the best of our knowledge, no similar studies are currently ongoing. Likewise, we found no studies on piritramide versus morphine effects on CTCs presence and/or CR.

We are aware that the evaluation of CTCs presence and dynamics in the perioperative period is not equivalent to clinical CR parameters, considering the importance of long-term factors involved (adjuvant therapy, lifestyle, and comorbidities). However, we believe that it can serve as a reasonably sensitive laboratory biomarker of the effects of perioperative factors on CR, unbiased to the influence of long-term factors. This approach should simplify the identification of techniques that support antimetastatic immune responses and decrease CTCs/DTCs numbers and/or invasivity, mainly in the vulnerable postoperative period. Such techniques should diminish the risk of CR, potentially reducing morbidity and improving survival without additional expenses or burdens for the patients.

## Methods

The study protocol has been prepared using the SPIRIT 2013 Statement guidelines [39] and in full concordance with the Declaration of Helsinki.

### Project objectives

The aim of the project is to identify optimal analgesia techniques for CR prevention in open radical CRC surgery. Also, the aim is to elucidate the mechanisms of metastasis with regard to the expression and activity of various receptor subtypes in cancer tissues and the effects of morphine and piritramide on these receptors. Therefore, we intend to perform a prospective, randomized, controlled, multicenter trial comparing the effects of epidural, morphine- and piritramide-based analgesia on CTCs presence and dynamics in radical open CRC surgery. Correlations between the type of PA and the number of CTCs in the early postoperative period will be studied. We formulated the following working hypotheses:- Different methods of analgesia affect CTCs presence and metastasis following CRC surgery.- In CRC patients, the number of CTCs in the early postoperative period correlates positively with metastasis and negatively with survival.- Epidural analgesia has favorable effects on CTCs presence and metastasis compared with morphine- and piritramide-based PA.- Piritramide-based PA has favorable effects on CTCs presence and metastasis compared with morphine-based PA.

### Primary outcome

The difference between the number of CTCs prior to surgery and 2—4 weeks after the surgery.

### Secondary outcomes

Pain intensity will be assessed in regular intervals (4 h) during the first 72 postoperative hours using the Numerical Rating Scale (NRS). Other secondary outcomes include hemodynamic stability, the incidence of ileus, and incidence of postoperative nausea and vomiting.

The last secondary outcome is the expression and activity of various receptor subtypes in cancer tissue.

### Inclusion criteria

- Patients indicated for open radical CRC surgery- Both genders – males and females- Adults – aged > 18 years- Capabilities to understand and sign the informed consent

### Exclusion criteria

- Intolerance or allergy to study drugs- A history of previous colorectal surgery- Active neoadjuvant therapy prior to enrollment- Contraindications to epidural analgesia- Another malignancy not in permanent remission- Chronic opioid medication or opioid administration within 7 days preoperatively- Immunosuppressive or corticosteroid therapy- Surgery within 30 days preoperatively (except for minor procedures)- Chronic or acute infections

### Clinical trial design

The design of the clinical trial is described in detail in Fig. 1 representing the flowchart of the study.

**Fig. 1 Fig1:**
[figure not shown]
Study flowchart

### Sample size selection

Power analysis and sample size calculation stem from our prospective pilot data in 57 patients (17 patients with morphine, 19 patients with epidural, and 21 patients with piritramide analgesia). In this pilot study, we found a significant reduction in the number of CEA-mRNA positive CTCs (CEA = carcinoembryonic antigen) in systemic blood in 35% of piritramide- versus morphine-receiving patients. To confirm this effect, we expect a 35% decrease in CTCs in systemic blood in this ongoing study. We aim to demonstrate the effect in the epidural/piritramide analgesia groups at the level of 20%. Based on the power of 0.8 and the first type error of 0.05, we calculated the minimum number of subjects in the group to be 37. In order to compensate for a potential dropout of 10%, we decided to enroll minimum 40 patients per group, i.e. minimum 120 patients in total.

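### One sample size, 37 per group at 80% power, is attached to two effects (35% and 20%) without saying which produced it, and its pilot input is not the primary outcome

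*Protocol article*

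**What the plan says.** All of the sizing is in the protocol article's Sample size selection section. It rests on a pilot of 57 patients (17 morphine, 19 epidural, 21 piritramide), in which "we found a significant reduction in the number of CEA-mRNA positive CTCs"; the size of that pilot result is worded as "in systemic blood in 35% of piritramide- versus morphine-receiving patients". The next step restates this as a planning value for the trial: "we expect a 35% decrease in CTCs in systemic blood in this ongoing study". A second target follows: "We aim to demonstrate the effect in the epidural/piritramide analgesia groups at the level of 20" percent. The paragraph ends with one result, for 80% power and a type I error of 5%: "we calculated the minimum number of subjects in the group to be 37".

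The Primary outcome section defines what will be compared: "The difference between the number of CTCs prior to surgery and 2—4 weeks after the surgery". The section on sample collection and molecular biology analysis says how that number is obtained: fluorescence microscopy on the CytoTrack platform, classifying cells by morphology, nucleus and antibody staining (CK20 and EpCAM positive, CD45 negative). The Methods of data stewardship and analysis section offers ANCOVA, repeated ANOVA or rank tests for the change in count. No test, base rate or SD is linked to the figure of 37.

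**The concern.** Two things do not fit together.

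First, two effects of different size share one sample size and one power. On a common scale with a common variance or base rate, a number that gives exactly 80% power for 35% gives much less for 20%. A number that gives 80% for 20% gives far more than 80% for 35%. The reader cannot tell which case applies.

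Second, the input changes its nature within the paragraph. A reduction seen in a percentage of patients is one quantity, and a percentage fall in the number of cells is another. The pilot marker (CEA-mRNA) also differs from the trial's read-out (an immunofluorescence cell count), and the outcome is a within-patient change.

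What is at stake is how a null result can be read. The Project objectives section lists epidural versus both opioids, and piritramide versus morphine, as working hypotheses. If a non-significant result in the 20% comparison is read against 80% power, it will look like evidence of no difference. If the true power was nearer one third, it carries little information.

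**Working it through.** **Inputs from the protocol:** alpha 0.05; power 0.80; 37 per group; effects 35% and 20%; equal groups.

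**Assumed, because not stated:** two-sided tests, pairwise comparisons without multiplicity adjustment, and the base rates and SDs shown below.

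**1. Can 37 be reproduced?** Not from the stated inputs alone. Several routes reach it once something is assumed.

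- *Two proportions, 35 points apart.* n = [1.960·√(2p̄(1−p̄)) + 0.842·√(p₁(1−p₁)+p₂(1−p₂))]² / δ². For 0.65 vs 0.30: (1.960·0.7062 + 0.842·0.6614)² / 0.1225 = 3.767/0.1225 = 30.75. The continuity correction gives (30.75/4)·[1+√(1+4/(30.75·0.35))]² = 36.2, so 37. The same holds for 0.70 vs 0.35. Without the correction the maximum over all base rates is 31.
- *Three-group one-way ANOVA, f = 0.30.* 110.1 in total, so 37 per group.
- *Difference in means, t test.* 37 per group gives 80% power at a standardised difference d = 0.660. A 35% fall meets this if the SD is 0.35/0.660 = 0.53 of the mean, and a 20% fall if it is 0.20/0.660 = 0.30 of the mean.

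**2. If 37 was sized on 35%, what is left for 20% on the same scale?**

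| Scale | SD implied by 37 for 35% | d for 20% | Power at 37 | n per group for 80% |
|---|---|---|---|---|
| Linear count | 0.35/0.660 = 0.530 | 0.20/0.530 = 0.377 | 36% | 111.3, so 112 |
| Log count | −ln(0.65)/0.660 = 0.431/0.660 = 0.652 | 0.223/0.652 = 0.342 | 31% | 135.2, so 136 |

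**3. A 20-point difference in proportions, by base rate** (the two-proportion formula above; power without continuity correction):

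| Rates | n, uncorrected | n, corrected | Power at 37 |
|---|---|---|---|
| 0.25 vs 0.05, or 0.95 vs 0.75 | 49 | 59 | 68% |
| 0.30 vs 0.10, or 0.90 vs 0.70 | 62 | 72 | 58% |
| 0.60 vs 0.40 | 97 | 107 | 40% |
| 0.20 vs 0, or 1.00 vs 0.80 | 35 | 44 | 83% |

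Power reaches 80% only at the two extremes, and there only without the correction. At the rates where 35 points gives exactly 37 (0.65 to 0.70), a 20-point difference has 41 to 42% power.

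**4. If 37 was sized on 20%.** With an SD of 0.30 of the mean, power is 81% for a 20% fall and above 99% for a 35% fall. Both effects would then be covered.

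**5. The count outcome without a known SD.** Power at 37 per group for a 35% fall, by SD as a fraction of the mean: above 99% at 0.3, 84% at 0.5, 32% at 1.0, 12% at 2.0. The unstated SD decides the answer.

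**The case against.** The strongest defence is that the 20% target stands directly before the figure of 37, and sizing on the smaller effect is ordinary practice. Step 4 shows that one number can then serve both effects. The pilot covered all three arms and may have supplied an SD, and a journal article need not print every input. This stands: a shortfall for 20% cannot be asserted outright, and an unprinted SD is not in itself a fault. It does not answer the visible problem. The only percentage traced to the pilot is the 35%, that result is on a different marker, and an SD as small as 0.30 of the mean appears nowhere in the text.

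A reader might infer that 37 can only have come from a 35-point difference in positivity rates. The document does not support that. The match needs an assumed base rate and a continuity correction, and step 1 shows other routes, including an ANOVA, which belongs to the analysis family the protocol names.

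A reader might also infer that the trial has been shown to lack 80% power for its primary outcome, or that no count variance was used. Neither can be known. The power is unsupported, which is weaker than disproved.

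Finally, the 20% sentence names no comparator or scale. It may mean epidural versus piritramide, or each of them versus morphine.

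**Conclusion.** The point holds in conditional form. The protocol gives one sample size for two effects without saying which it belongs to, and its pilot quantity is neither the marker nor the measure of the primary outcome. The stated 80% power is therefore not established for the change in CytoTrack count.

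The size depends on the unstated basis. If 37 came from the 35% effect, a 20% effect has about 31% (log) to 36% (linear) power as a fall in a count, and 40 to 68% as a difference in proportions with the higher rate between 0.25 and 0.95. These figures assume two-sided pairwise tests at 0.05 and the same scale and variance for both effects. If 37 came from a 20% fall with an SD near 0.30 of the mean, there is no shortfall, but the document gives nothing to support that SD.

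**What to change.** Revise the Sample size selection section; no extra patients are needed.

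1. State the effect, comparison, scale, test and base rate or SD that produced 37, and confine the 80% power claim to that comparison. The authors must supply these inputs; they should not be back-fitted from the figure.
2. For the other effect, replace the implied 80% with its actual power, or with the detectable difference: about 0.66 SD per pairwise comparison at 37 per group.
3. Restate power for the change in CytoTrack count, using its SD computed from pooled data blind to arm. State separately what the pilot showed on the CEA-mRNA marker.
4. If the 20% comparison proves underpowered, report it as an estimate with a confidence interval, and say that a non-significant result will not be read as no difference.

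The cost is rewording and one blinded variance calculation. The downside is that the stated power will probably look less favourable.

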### Perioperative period

Patients are administered 400 ml/50 g carbohydrate pre-surgery drink, premedicated and anesthetized according to the standardized protocol which defines: perioperative medication, fluid therapy, hemodynamic goals and management, diuresis, core temperature, transfusion threshold, and postoperative nausea, and vomiting prevention. The protocol also defines analgesia corresponding with randomization (including a detailed standard of care for thoracic epidural analgesia). All the data are recorded including the length of anesthesia and surgery, and a brief description of the type of surgery and observed radicality.

Postoperative care is standardized including postoperative analgesia corresponding with randomization, hemodynamic optimization, fluid therapy and transfusions, glycemic control, and postoperative nausea and vomiting management.

A detailed description of perioperative and postoperative management in all three arms of the study is displayed in Fig. 2. The patients with insufficient pain relief on the protocol medication will be provided rescue multimodal analgesia with a strong opioid and will be excluded from the final analysis of the CTCs.

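### Enrolling 40 per group does not cover the stated 10% dropout on a required 37: it leaves 36, a shortfall of one patient per group and about one point of power

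*Protocol article*

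**What the plan says.** Sample size selection takes 80% power and a type I error of 5% and reports the result: "we calculated the minimum number of subjects in the group to be 37". The next step inflates this figure for losses: "In order to compensate for a potential dropout of 10%, we decided to enroll minimum 40 patients per group". Over the three arms this makes at least 120. The Methods paragraph of the abstract gives the total without the qualifier: "We intend to enroll 120 patients in four centers in this prospective randomized controlled trial".

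One more sentence bears on the evaluable number. Under Perioperative period, patients whose pain is not controlled on the protocol medication, and who therefore receive rescue analgesia, "will be excluded from the final analysis of the CTCs". The CTC count is the primary outcome. Sample size selection does not mention these exclusions and does not define dropout.

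**The concern.** The section calls 37 per group a minimum, and presents 40 as the enrolment that protects it against 10% dropout. If 40 falls below 37 once that dropout is applied, the stated enrolment does not do what the sentence says, on the plan's own inputs. What is at stake is whether the trial, run exactly as described, can expect the evaluable number behind its 80% power. A second question is whether any other loss from the CTC analysis has to come out of the same allowance.

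**Working it through.** **Inputs, all from Sample size selection:** required evaluable number 37 per group; dropout 10%; enrolment 40 per group and 120 in total; power 0.8; type I error 0.05. The trial has three arms (Recruitment and randomization).

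**Can the plan's figure of 40 be reproduced?**
- Standard inflation, n/(1 − d): 37/0.9 = 41.1, rounded up to 42.
- Common shortcut, n × (1 + d): 37 × 1.1 = 40.7, rounded up to 41.
- Forty appears only if 40.7 is rounded down. That may be how it arose, but the document does not say.

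**Check in the other direction, evaluable = enrolled × 0.9:**

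| Enrolled per group | Expected evaluable at 10% dropout | Reaches 37? |
|---|---|---|
| 40 | 36.0 | no |
| 41 | 36.9 | just short |
| 42 | 37.8 | yes |

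**Dropout that 40 does cover:** (40 − 37)/40 = 7.5%.

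**Totals.** 3 × 37 = 111 evaluable are required. From 120 enrolled, 120 × 0.9 = 108 remain. Three equal groups of 42 make 126. Inflating the total without rounding up per group gives 111/0.9 = 123.3, so 124. Either figure exceeds 120.

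**Effect on power.** The section gives no standard deviation, control rate, test or sidedness, so the 37 cannot be rebuilt. Only the relative loss can be shown, by taking 37 per group as giving 80% power in a comparison of two groups.
- Two-sided normal approximation: implied standardized effect d = (1.960 + 0.842) × √(2/37) = 0.651. Power at 36 = Φ(0.651 × √(36/2) − 1.960) = 0.789.
- One-sided normal approximation: d = 0.578. Power at 36 = 0.790.
- Two-sided t-test: d = 0.660. Power at 36 = 0.789.

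All three give about 79%, a loss of about one percentage point.

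**Rescue exclusions.** No rescue rate is stated, and the text does not say whether the 10% includes these patients. If it does, the figures above are complete. If it does not, fewer than 36 per group are expected in the CTC analysis. The protocol gives nothing from which to calculate how many fewer.

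**The case against.** The strongest defence is that the error has almost no consequence. It amounts to one evaluable patient per group and one point of power, 10% is a round planning figure for a potential loss, and no conclusion of the trial turns on it. That stands, and it limits the weight of the point. It does not make the sentence right.

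A second defence is the word *minimum*: 40 is a floor, so enrolling 42 per group would comply. This holds only in part. The floor is itself the number said to absorb 10% dropout, and it does not. The abstract plans a flat 120.

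A third is that the power figures rest on an effect calibrated backwards from 37, while Methods of data stewardship and analysis lists ANCOVA, repeated-measures ANOVA and non-parametric tests. That is correct, so 79% should be read as a relative loss and not as the trial's actual power.

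A reader might go further and infer that rescue exclusions push the evaluable number well below 36, with a serious loss of power. The documents do not support this. It needs a rescue rate that they do not contain, and the 10% may already be meant to include these patients. Nor does the arithmetic show that the rescue exclusion should be dropped. Who belongs in the CTC analysis is a separate question about the analysis population.

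**Conclusion.** The point holds as an arithmetic error with a minor effect. On the plan's own inputs, 40 per group with 10% dropout gives 36 evaluable patients and not 37. Covering 10% needs 42 per group (126 in total), and the stated 40 covers 7.5%. The supported loss is one evaluable patient per group and about one point of power. The counts rest only on printed figures. The power statement also assumes that 37 per group gives 80%, which the stated inputs do not allow anyone to check. Whether rescue exclusions enlarge the shortfall is open, because the protocol does not say how they relate to the 10%.

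**What to change.** Correct the inflation sentence in one of two ways:
- Keep 40 per group (120), and state that this allows 7.5% dropout. Equivalently, state that 10% dropout leaves 36 evaluable per group and about 79% power. This costs one sentence and no patients.
- State 42 per group (126), which the existing *minimum* already permits, and change the total in the abstract to match. This costs six more patients.

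In either case, add a clause saying whether the 10% includes patients left out of the CTC analysis after rescue analgesia. If it does not, give the expected rate of these exclusions and the enrolment or power that follows. The clause costs nothing. Any further cost depends on a rate that only the sponsor can supply.
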